## Abstract

**Background:**

Mental health conditions impose a significant burden worldwide, often remaining untreated due to multiple demand- and supply-side barriers such as stigma, limited awareness, and poor access to services. Mobile-based interventions offer a scalable solution to address some of these barriers, including low rates of help-seeking. However, most evidence has emerged from high-income countries, with minimal research in the Indian setting, particularly among psychologically distressed individuals not currently seeking treatment.

**Objective:**

This study aims to evaluate the effectiveness of a minimally guided mobile app in promoting help-seeking behaviors among individuals experiencing self-reported common mental health concerns and significant psychological distress who are not currently engaged in formal treatment. Additionally, it will examine the utility of the intervention in reducing perceived barriers to seeking professional help for mental health, improving the inclination to seek help from mental health professionals, and alleviating psychological distress. Perceived benefits of using the app will also be documented.

**Methods:**

A parallel-arm randomized controlled trial will be used to evaluate the effectiveness of the minimally guided, indigenously developed mobile app in enhancing help-seeking behaviors among distressed, nontreatment-seeking adults. The intervention arm will receive a multimodule app while the active control will receive a mood-logging app. Assessments will occur at baseline, 5 weeks after the intervention, and at the 1-month follow-up using standardized self-report tools and additional items. The primary outcome will be actual help-seeking behavior in accessing mental health professionals, while secondary outcomes will include help-seeking inclination, perceived barriers, psychological distress, and perceived benefits.

**Results:**

The trial commenced in September 2025 and is currently in the recruitment and data collection phase. Participant enrollment is ongoing. Data collection is anticipated to be completed by July 2026, and findings from the study are expected to be disseminated through a peer-reviewed publication by December 2026.

**Conclusions:**

This study will provide contextually relevant insights into the utility of a minimally guided mobile app-based intervention in improving professional help-seeking among psychologically distressed, nontreatment-seeking individuals in India. Findings may inform the design and scaling of accessible digital interventions to bridge the mental health treatment gap in low-resource settings.

**Trial Registration:**

Clinical Trial Registry of India CTRI/2024/11/077461; https://tinyurl.com/2edf5a32

**International Registered Report Identifier (IRRID):**

DERR1-10.2196/85267

## Introduction

### Background

Despite the availability of effective treatments, common mental health problems such as depression remain highly prevalent, with a significant treatment gap persisting both globally and in India [1,2]. This has been attributed to both supply-side and demand-side barriers, such as poor access to mental health services, low mental health literacy, and stigma [3]. Noting that global efforts have disproportionately focused on specialist psychiatric care, the World Health Organization model of the optimal mix of services highlights the importance of investing efforts in the development of low-intensity interventions such as self-help and community support for milder severity of problems [4]. In addition to strengthening access to mental health services, research highlights the need for scalable interventions that address demand-side barriers, including efforts to improve mental health literacy and encourage help-seeking [2-4]. In the context of mental health, help-seeking has been defined as “an adaptive coping process—that is, the attempt to obtain external assistance (from informal and formal sources of help) to deal with a mental health concern” [5]. A variety of interventions have been developed to improve mental health help-seeking, often targeting either an individual’s inclination (the willingness to seek help) or behavior (the actual act of seeking care) [6].

Digital mental health interventions have emerged as promising avenues for delivering low-intensity self-help strategies, enhancing mental health literacy, and improving help-seeking due to advantages such as scale, privacy, and ease of access [7]. There is burgeoning research on app-supported interventions for various mental health problems across diverse populations, suggesting their utility as scalable and accessible tools to address the unmet mental health needs of populations [8-11]. However, most research on digital interventions originates from high-income countries, with a notable scarcity of studies from low- and middle-income regions [12-14].

There is a scarcity of studies from the Indian context on the utility of mobile app-based interventions for common mental health concerns, and particularly for enhancing help-seeking [15-17].

A recent systematic review of mental health apps accessible to Indian users through major app stores examined 350 apps in detail [18]. Out of these, the largest numbers were contributed by apps retrieved using the keywords “depression,” “anxiety,” and “mental health.” Only 17.7% of the reviewed apps originated from Asia, underscoring the limited regional representation in digital tools available to Indian users. This review highlighted several critical concerns. Notably, 65% of apps did not mention any involvement of mental health professionals in their development. Only 11% referenced an evidence base, and issues related to privacy and user safety were also prominent. Although about 40% of apps included pointers to seek professional help, these were often limited to generic disclaimers. Proactive nudges or motivational prompts to seek help appeared in fewer than a quarter of the reviewed apps. These observations point to critical gaps in the development of mental health mobile apps for Indian users.

Against this background, an indigenous mobile self-help app, called MindNotes, was developed for the Indian context, informed by prior research and rooted in the clinical experience of mental health professionals working in the country, and based on formative work [19]. The app evolved through multiple iterations and user feedback. It is among the first indigenous apps available in English, as well as 2 Indian languages (Kannada and Hindi), thus aiming to address linguistic diversity in the country to some extent. It is designed for individuals experiencing psychological distress or common mental health symptoms who may be uncertain about the nature or severity of their concerns, or ambivalent about seeking professional support. It is a multimodule app containing sections aimed at (1) improving self-awareness about the nature and severity of common mental health concerns and receiving recommendations on the need for professional help (self-discovery section), (2) identifying and reducing barriers to seeking professional help (breaking barriers section), and (3) improving knowledge and skills in using self-help strategies for common mental health concerns, such as managing worry and self-criticality (self-help toolkit). Additional sections include the coping with the crisis section, which provides simple strategies for dealing with a crisis and accessing helpline numbers, and the professional connect section, which clarifies general doubts and queries regarding mental health and the process of professional consultation, offers basic support, and provides nudges to seek professional help via a note-sharing space.

The app involves interactive elements and includes quizzes, personalized feedback, motivational videos, reflective exercises, self-help strategies, and guidance related to common mental health concerns. A preliminary trial of this app indicated encouraging trends in the perceived relevance and potential usefulness of its various sections and their utility in improving mental health awareness and motivation to seek professional consultation for self-reported depressive and anxiety symptoms [20].

Unguided digital interventions tend to result in low engagement rates that can influence outcomes [21,22]. The MindNotes app provides minimal guidance and support through its professional connect module for users. In the experience of the authors, the content shared by users on the professional connect section underscores its value in reaching distressed, nontreatment-seeking individuals seeking information, support, and guidance. Its self-discovery and breaking barriers sections are aimed at helping users gain a better understanding of their depressive or anxiety symptoms and overcome hesitations and barriers to seeking professional help when required. Thus, the app has the potential to strengthen help-seeking inclinations and behaviors, while also offering self-help strategies for common mental health concerns that may contribute to reductions in distress. Moreover, it is well recognized that interventions to improve help-seeking are likely to be useful when these are delivered as targeted interventions for those experiencing symptoms or significant distress [23].

This study is aimed at examining the effectiveness of the MindNotes app in improving help-seeking in a sample of distressed nontreatment seekers by using a randomized controlled design.

### Objectives

The objectives of the study are to evaluate the effectiveness of the minimally guided MindNotes app in enhancing professional help-seeking behaviors among individuals with self-reported common mental health concerns and significant psychological distress who are not currently engaged in treatment. Additionally, the study aims to examine the utility of this app in improving the inclination to seek help from mental health professionals, reducing perceived barriers to seeking professional help for mental health, reducing psychological distress, and documenting perceived benefits of using the app. Help-seeking behavior is the primary outcome variable, while help-seeking inclination, barriers to seeking professional help, and psychological distress are the secondary outcome variables.

## Methods

### Study Design

This study will use a parallel-arm randomized controlled design with assessments at baseline, after the intervention, and at follow-up to compare the effectiveness of the minimally guided MindNotes app-based intervention against an active control condition involving a basic mood-logging intervention described further. The trial will be conducted over a period of 4 weeks, with reminders provided at specific intervals to support participant engagement in both the arms. Participants will complete the postintervention assessment at the conclusion of the 4‑week intervention phase, with a follow-up assessment scheduled 1 month after the postintervention assessment. The study design and reporting will adhere to the SPIRIT (Standard Protocol Items: Recommendations for Intervention Trials) guidelines for randomized trials of digital health interventions [24].

### Recruitment and Sampling

Participants will be recruited from the community through a multipronged strategy combining online and offline dissemination. This will include social media outreach, online announcements, and dissemination of posters in colleges, workplaces, and community locations. The inclusion criteria for the study are individuals aged 18 years and older, of all genders, fluent in English or Kannada, with at least 10 years of formal education, comfortable using a smartphone, experiencing self-reported current depressive or anxiety symptoms for 2 weeks or longer, and scoring 20 or above on the Kessler Psychological Distress Scale (K10) [25]. Participants will be excluded if they are currently receiving pharmacological treatment for any mental health condition, have attended 3 or more psychotherapy or counseling sessions in the past 3 months, or are presently engaged in counseling or psychotherapy. Individuals currently using any other mental health app, or those not amenable to participating in the study as assessed in a brief telephonic interview, or those having significant suicidal ideation as determined by responses on 2 items pertaining to the frequency and controllability of suicidal thoughts in the past 1 month, will be excluded from the study.

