### Procedure

Participants will be randomized into either the intervention or control group in a 1:1 ratio, using a computer-generated randomization sequence. The randomization list will be generated by the study supervisor. Stratified randomization will be used based on age group (18-35 years and 36 years and above) and gender to ensure balance across key demographic variables.

A brief telephonic interview for eligibility screening will be conducted after all other questionnaires are completed. This call allows the researchers to clinically assess the current mental state and amenability to take part in the study process, inquire whether participants have sought consultation for any psychiatric problem in the past or recent times, and confirm willingness to participate.

Eligible participants will receive an introductory call informing them of their group allocation and guiding them on how to begin engagement with the study activities. All assessments will be conducted through an online survey, and feedback will be obtained over the phone from both groups at the end of the 4-week intervention period. A follow-up telephonic interview will be conducted 1 month after the postintervention assessment to ascertain help-seeking inclination and help-seeking behavior. The flow of the study is depicted in Figure 1.

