### Ethical Considerations

The study has been approved by the Institutional Ethics Committee of the National Institute of Mental Health and Neurosciences, Behavioural Science Division (NIMHANS/45th IEC [BEH.SC.DIV.]/2024/22.03.2024) and is prospectively registered in the Clinical Trials Registry of India. Informed consent will be obtained from individuals prior to recruitment, and no compensation will be offered to participants for taking part in the study. Baseline and postintervention surveys will be administered electronically via REDCap (Research Electronic Data Capture), a secure, web-based platform for data collection and management, hosted at the first author’s institution. The digital apps used in the study incorporate “privacy by design” and use technical and policy safeguards to ensure the security of the data and protect the privacy of users. User passwords are stored securely through encryption. Personally identifiable information elements (email addresses and phone numbers) are stored in encrypted form and are decrypted within the program when needed. The data obtained from the participants through text messages and emails will be backed up and stored on a password-protected system.

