Only authorized research team members will have access to identifiable data. WhatsApp messages will be standardized and delivered via a business account, with no sensitive information exchanged. Referral-related guidance to seek appropriate professional help will be provided for all individuals who are not eligible for participation and those who decline participation. Participants will receive appropriate mental health service suggestions based on their needs and preferences at any point in time if required. Participants will be free to opt out of the study at any point. A telephone session will be held with those who score above the cutoff on suicidality to guide, motivate, and support them in seeking professional help. They will not be part of the study. Helpline numbers are also available in the app and will be shared with these individuals for use as per their needs. These individuals will also be informed that they can reach out to the researcher again if they need more referral options at a later point. The active control group will be debriefed at the end of the study and provided information and links to the MindNotes app. In addition, they will be free to contact the researcher for guidance or professional help at any point during the intervention period, if they so desire.

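### The app-use exclusion names only other mental health apps, so read literally it leaves current MindNotes users eligible; any who enrol would attenuate the comparison

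*Protocol article*

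**What the plan says.** Under Recruitment and Sampling, the only criterion on app use excludes "Individuals currently using any other mental health app". MindNotes is not named there, and no other criterion concerns it. The screening call described under Procedure covers mental state and amenability, and is to "inquire whether participants have sought consultation for any psychiatric problem in the past or recent times, and confirm willingness to participate"; app use is not among the topics mentioned.

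Three statements in the Background bear on whether such users exist:

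- On availability: "It is among the first indigenous apps available in English, as well as 2 Indian languages". The two are Kannada and Hindi, and the trial recruits people fluent in English or Kannada.
- On earlier research use: "A preliminary trial of this app indicated encouraging trends".
- On existing users: "the content shared by users on the professional connect section underscores its value in reaching distressed, nontreatment-seeking individuals".

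Under Ethical Considerations, "The active control group will be debriefed at the end of the study and provided information and links to the MindNotes app".

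**The concern.** In a MindNotes trial, the natural meaning of an exclusion for other apps is apps other than MindNotes. A person already using MindNotes therefore passes the rule as written. Past use is not covered on any reading, because the rule concerns current use only.

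The Background describes existing users as distressed people not in treatment, which is the population the trial recruits. Deferring the MindNotes link to debriefing shows that controls are intended to be unexposed, and the eligibility wording does not protect that intention.

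A control who already uses MindNotes may show more help-seeking than an unexposed control. A prior user in the app arm may gain less than a new user. Both shrink the difference on the primary outcome. The sample size targets 80% power and has little slack to absorb this.

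**Working it through.** **Inputs from the protocol.** Power Calculation: help-seeking 25% vs 10%, 80% power, 5% significance level, up to 33% attrition, 150 per group. Procedure: 1:1 allocation. Data Analysis Plan: 2-sided .05, chi-square test, completer analysis.

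**Input not in the protocol.** The share *f* of participants who already use MindNotes. I take 0% to 20% as an illustrative range.

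**Reproducing the planned size.** With p1 = 0.25, p2 = 0.10 and mean 0.175, the two-proportion formula with pooled variance and no continuity correction is

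n = [1.96 × √(2 × 0.175 × 0.825) + 0.84 × √(0.25 × 0.75 + 0.10 × 0.90)]² / 0.15² ≈ 99.5, so 100 per arm.

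Allowing for attrition, 100 / (1 − 0.33) = 149.3, so 150 per arm. The protocol's figure reproduces exactly, and the sample size is not in question.

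**Model A: exposed controls reach the full 25%.** Control rate = 0.10 + 0.15 × *f*, app arm 25%.

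**Model B: exposed controls get half the effect.** Control rate = 0.10 + 0.075 × *f*, app arm 25%.

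**Model C: prior users do not respond and stay at 10% in both arms.** App-arm rate = 0.25 − 0.15 × *f*, control 10%.

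Exact power of the 2-sided Pearson chi-square test (no continuity correction), 100 completers per arm:

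| Share *f* | A: control rate | A: power | B: power | C: power |
|---|---|---|---|---|
| 0% | 10.00% | 81.6% | 81.6% | 81.6% |
| 1% | 10.15% | 80.6% | 81.1% | 80.9% |
| 2% | 10.30% | 79.7% | 80.6% | 80.2% |
| 5% | 10.75% | 76.6% | 79.2% | 78.1% |
| 10% | 11.50% | 71.1% | 76.6% | 74.2% |
| 20% | 13.00% | 59.2% | 71.1% | 65.3% |

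The normal approximation for model A gives 80.2%, 75.2%, 69.8% and 58.1% at 0%, 5%, 10% and 20%. The levels are slightly lower and the losses nearly the same.

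**Why the direction is attenuation.** Randomization spreads prior users over both arms in expectation. If they have the same help-seeking rate in either arm, whatever that rate is, the expected difference becomes 15 points × (1 − *f*): 14.25 points at 5%, 13.5 at 10% and 12 at 20%. Models A and C are the cases where that common rate is 25% and 10%.

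**The case against.** The strongest reply is that this is one loose word in a condensed article. The criteria do not say that MindNotes users are welcome, the debriefing arrangement shows the opposite intention, and the full protocol or screening form may ask about MindNotes. That stands as far as intent goes. A reader might infer that the protocol permits enrolment of existing users, or that nothing in the trial would detect them; the article does not establish either. What remains is that the rule as published does not exclude them.

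A reader might also infer that the comparison is in fact diluted, or that a null result could not be told apart from contamination. The documents do not support this. The Background gives no number of users, and they may largely be participants of the preliminary trial. Nothing shows how many would respond to recruitment. At 1% to 2% the loss is only about 1 to 2 points of power.

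It is likewise too strong to say that an exposed control has already had the tested intervention. The tested package includes four weekly personalized notes, two reminders and a request to work through particular sections over 4 weeks. Self-directed use is not shown to include these. Eligibility also selects against responders: someone whom the app had moved into ongoing treatment would be excluded, so prior users who qualify have remained untreated despite exposure. The full 25% for exposed controls is therefore close to an upper bound. This reduces the loss but need not remove it, because prior users who do not respond attenuate the difference through the app arm (model C). If they still benefit from the personalized notes, the loss is smaller again.

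Finally, matching participants against MindNotes accounts is not something the documents show to be necessary or covered by consent. They say only that "Personally identifiable information elements (email addresses and phone numbers) are stored in encrypted form", and people may register with different details.

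**Conclusion.** The point holds as a minor eligibility correction. Read literally, the exclusion leaves current MindNotes users eligible, the Background shows that such users exist in the target population, and the design intends controls to be unexposed until the end of the study.

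The consequence is conditional on prior users enrolling, and it is attenuation with lost power, not imbalance between arms. The loss in exact power is about 2 points at a 2% share, 5 at 5%, 10 at 10% and 22 at 20%. These figures assume 100 completers per arm, planning rates of 25% and 10%, and exposed controls at the full 25%. With half the effect the loss is about 2 points at 5% and 5 at 10%. The share itself is an assumption. The planned 150 per group is correct for its stated inputs.

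**What to change.** - Reword the exclusion to current use of any mental health app, including MindNotes.
- Ask about current and past MindNotes use at screening and record the answer.
- Record MindNotes use in both arms at the postintervention and follow-up assessments.
- Do not remove anyone from the primary comparison because of MindNotes use: keep everyone randomized in it. Add a sensitivity analysis without participants who report MindNotes use before randomization. Because that exclusion rests on a pre-randomization fact, it adds no selection of its own. It does not make the result unbiased, since the primary outcome is a completer analysis and attrition bias remains.
- Matching against MindNotes accounts is optional, and only where participants' consent covers it.

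The cost is a few recruits and one or two added questions. Recruitment is under way, so the new wording helps only future recruits. For people already enrolled, asking about earlier MindNotes use at their remaining assessments would still show how large the share is.
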